### Statistical analysis

At baseline, half-way (8 weeks) and at the end of the study (16 weeks) outcomes are measured (see supplement 5 for a specification of the measurements).

After conclusion of the randomized controlled trial, data will be cleaned, verified by two researchers, and inspected for errors, inconsistencies, and incomplete information. Outliers will be inspected and corrected if necessary.

Primary outcomes DAS28, RA risk-scores, and WOMAC (all continuous variables) at 8 and 16 weeks in the intervention group will be compared with outcomes at 8 and 16 weeks in the control group, adjusted for baseline scores. Intention-to-treat analyses will be performed, with additional per-protocol analyses. For the analyses, a repeated measures mixed model will be used with random effect for the subjects and fixed effects for group (intervention or control) and baseline values for DAS28, RA risk-score, or WOMAC.

Secondary outcome measures (physical function, fatigue, pain interference, depression, waist circumference, fat mass, blood pressure, LDL, HDL, triglycerides, fasting glucose and ESR) will be analyzed the same way as the primary outcomes. Statistical tests will be limited to primary and secondary outcomes. For other outcomes, descriptive statistics will be used. We will analyze microbiome, remaining metabolic and stress-related outcomes separately and report results in dedicated articles.

In the extension study, the primary and secondary outcomes of the intervention study will become secondary outcomes, and adherence will be the primary outcome. These outcomes are analyzed in the same way as the intervention study, using the baseline, halfway, and end measurements from the 16-week intervention program, as well as 6-, 12-, and 18-month and end (24 month) measurements of the extension study. Intention-to-treat analyses will be performed, with additional per-protocol analyses. Since the extension study is observational, a within-subject analysis will be performed using a repeated measures mixed model with random effect for the subjects and fixed effects for baseline values.

*P* values < 0.05 will be considered to be significant.

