### Measurements

#### Primary outcome measures

Main endpoints are the differences between mean changes in the intervention versus control groups from 0 to 16 weeks in:
RCT 1: the DAS28 based on erythrocyte sedimentation rate (ESR), number of swollen joints and tender joints and general health based on the score on a visual analog scale [49] (measured by a blinded research nurse) for RA patients.RCT 2: the RA-risk score (combined score based on RA prevalence in first degree relatives, alcohol consumption, duration, intermittency and location of symptoms, pain, morning stiffness, self-perceived swelling of joints and antibody status) [38] in ACPA-positive arthralgia patients. If a subject develops RA during the study, the RA-risk score will be set to 13 points, the highest possible score.RCT 3: scores on pain, stiffness, and function, combined in the Western Ontario and McMaster Universities Osteoarthritis Index (WOMAC) index [50] for OA patients, measured by the WOMAC questionnaire [51].

Main endpoint for the 2-year extension study for all three groups is the change in adherence from 0 to 24 months, based on an adapted version of the *Lifestyle index adherence score* as developed by Ornish et al [52]:
$$ \left(\mathrm{t}+\left(\left[\mathrm{u}/6+\mathrm{v}/60\right]/2\right)+\left(\left[\mathrm{x}/5+\mathrm{y}/150\right]/2\right)+\mathrm{z}\right)/4 $$

In which *t* = attendance meetings, *u* = stress reduction activities days per week, *v* = stress reduction activities minutes per week, *x* = exercise days per week, *y* = exercise minutes per week, and *z* = adherence to diet.

Adherence to diet (*z*) is defined as ((grams of fiber per 1000 kilocalories/14) + (10/en% SFA))/2 whereby “en% SFA” is defined as the percentage of total kilocalories a day from saturated fatty acids (SFAs). In the original model by Ornish, *z* was defined by total fat and cholesterol intake. Since our protocol is not based on a low-fat WFPD, we changed these vectors into fiber and saturated fatty acids (SFAs) as indicators for a WFPD.

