### Sample size calculation

Based on *α* = 0.05 and power (1-β) = 0.80, effects ranged from 0.4 to 1.0 decreases for the DAS28 (estimated from component data of the DAS28 in the case of the trial by Kjeldsen Kragh et al.) with standard deviations (SD) ranging from 0.6–1.0 [12, 14]. The minimal clinically important improvement (MCII) in the DAS28, however, increases with higher baseline values and vice versa [60]. In the range of our inclusion criterion of DAS28 (between 2.6 and 5.1), the MCII is 0.8. Sköldstam et al. reported a difference in the DAS28 of 0.5 in 12 weeks [14]. In our 16-week study, we expect an additional effect on top of that provided by diet alone, due to the combination with exercise and stress management. Based on clinically relevant effect sizes of delta 0.8 with a SD of 1.2 for the DAS28, *α* of 0.05, and *β* of 0.2, we need a sample size of 56.

For OA patients, we found effects ranging from 2.2 to 2.8 for WOMAC pain (OA) and 5.7 to 10 for WOMAC function (OA) and standard deviations (SD) ranging from 0.4 to 0.6 with an exceptional 3.1 for WOMAC pain and 1.4 to 3.1 with an exceptional 10.9 for WOMAC function [15, 61, 62]. Based on these studies, we estimated that a power of 0.80 is feasible with a total of 60–70 subjects (intervention + control group) and planned to aim for 80 subjects for both RA as well as OA patients (total 160 patients) based on a possible dropout rate of approximately 20%.

For patients with ACPA-positive arthralgia, we added a pilot group of 16 participants (*n* = 8 intervention group, *n* = 8 waiting-list control group).

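### The listed terms of the primary mixed model pool weeks 8 and 16, so the group coefficient does not isolate the declared 0 to 16 week endpoint

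*Protocol article*

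**What the plan says.** Under Primary outcome measures the protocol article fixes the time frame of its main endpoints: "differences between mean changes in the intervention versus control groups from 0 to 16 weeks". The measures are DAS28 (RCT 1), the RA-risk score (RCT 2) and WOMAC (RCT 3).

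Under Statistical analysis, the primary outcomes "at 8 and 16 weeks in the intervention group will be compared with outcomes at 8 and 16 weeks in the control group". Baseline enters as a covariate. The terms given for the repeated measures mixed model are "random effect for the subjects and fixed effects for group (intervention or control) and baseline values" of the outcome concerned. Secondary outcomes are to be handled in the same way.

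The section lists no fixed effect for visit and no group-by-visit interaction, and it does not say which contrast from the model is the primary result.

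**The concern.** The endpoint section points to one time, week 16. The model takes two post-baseline visits per patient and has one group coefficient to describe both. That coefficient mixes the half-way effect with the final effect.

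The programme is taught over 16 weeks in 10 group meetings, so an identical effect at both visits cannot be taken for granted. If the effect is still building at week 8, the reported figure falls short of the 16-week effect; if it fades after week 8, the figure exceeds it. For RCT 1 the result will be read against 0.8, which the article gives as the minimal clinically important improvement in its DAS28 range, so a pooled figure could be set against a threshold meant for the final effect. The same model is planned for the primary outcome of all three RCTs.

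**Working it through.** **Inputs from the article.** "Based on clinically relevant effect sizes of delta 0.8 with a SD of 1.2 for the DAS28"; alpha 0.05; beta 0.2; 1:1 allocation; 80 patients planned for RA with about 20% dropout, hence 80 × 0.8 = 64 completers, 32 per arm.

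**Assumptions (not in the article).** The week 8 effect, as a fraction f of the week 16 effect, and the correlation ρ between the week 8 and week 16 values. Both are varied. Power below is two-sided at 0.05, t-based, with the same SD at both visits and no gain from baseline adjustment.

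**The plan's own figure.** The article concludes "of 0.2, we need a sample size of 56". By the normal approximation, n per arm = 2 × (1.2/0.8)² × (z_α + z_β)². One-sided: 4.5 × (1.645 + 0.842)² = 27.8, so 28 per arm and 56 in total, which matches. Two-sided: 4.5 × (1.960 + 0.842)² = 35.3, so 36 per arm and 72 in total. The sidedness is a separate matter and nothing below depends on it.

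**What the listed model estimates.** Let D8 and D16 be the baseline-adjusted group differences at the two visits. Group and baseline are constant within a patient. With a random intercept and both visits present for everyone, the fit therefore reduces to a regression of each patient's two-visit mean on group and baseline:

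group coefficient = (D8 + D16)/2 = D16 × (1 + f)/2.

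This equals D16 only when f = 1. A visit main effect alone would not change it; a group-by-visit term is needed to separate D16 from D8. If week 16 visits are missing, the weight moves towards week 8.

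**Size of the shift, D16 = 0.8.** Simulated means are from mixed-model fits with 40 per arm, complete data and 100 replicates per row.

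| Assumed week 8 effect | Target (D8 + D16)/2 | Simulated, model as listed | Simulated week 16 contrast, group-by-visit added |
|---|---|---|---|
| 0 | 0.40 | 0.38 | 0.77 |
| 0.2 | 0.50 | 0.50 | 0.80 |
| 0.4 | 0.60 | 0.59 | 0.79 |
| 0.6 | 0.70 | 0.68 | 0.77 |
| 0.8 | 0.80 | 0.78 | 0.77 |
| 1.0 | 0.90 | 0.91 | 0.79 |

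The listed model follows the average. The model with group-by-visit stays near 0.8 throughout.

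**Power.** The SD of a two-visit mean is 1.2 × √((1 + ρ)/2): 1.039 for ρ = 0.5 and 1.073 for ρ = 0.6. With 32 per arm, week 16 alone has non-centrality 0.8/(1.2 × √(2/32)) = 2.67 and power 0.75.

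| Week 8 effect (f) | Power of average, ρ = 0.5 | Power of average, ρ = 0.6 |
|---|---|---|
| 0 (0%) | 0.33 | 0.31 |
| 0.4 (50%) | 0.62 | 0.60 |
| 0.6 (75%) | 0.76 | 0.73 |
| 0.8 (100%) | 0.86 | 0.84 |

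**Break-even.** The average and week 16 alone have equal power when (1 + f)/2 = √((1 + ρ)/2), that is f = √(2(1 + ρ)) − 1. This gives √3.0 − 1 = 0.73 for ρ = 0.5 and √3.2 − 1 = 0.79 for ρ = 0.6.

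**The case against.** **The list may be condensed.** This is a journal article based on protocol version 7.0, which is not shown. Calling the model repeated measures, and naming both visits in both groups, fits a visit-specific comparison with a time factor behind it. That is fair: the text supports saying that no visit term is listed, not that none will be fitted. But the article itself chose to list the fixed effects, and followed as written the list misses its own endpoint. This is more than a detail left for later.

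**Multiplicity.** A reader might infer that, if each visit is compared separately, there are two primary tests at 0.05 without priority and an inflated false-positive rate. The document does not support this. The endpoint section already gives the 0 to 16 week change priority, and nothing says that week 8 alone could count as primary success. On the pooled reading there is one test, which is valid under no effect at either visit.

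**Loss of power.** A reader might also infer that pooling must cost power. The article gives neither the week 8 effect nor the correlation, and the sign depends on both: pooling gains power once roughly three quarters or more of the effect is present by week 8.

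**Scope.** RCT 2 is a pilot of 16 participants with no power claim, so the power figures do not bear on it. The visit schedule for the secondary outcomes is in figures and a supplement not available here; an outcome not measured at week 8 has no averaging problem.

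**Baseline adjustment.** It is not at fault. A baseline-adjusted difference at week 16 is a valid estimate of the difference in change.

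**Conclusion.** The mismatch between endpoint and model stands. The declared quantity is the 0 to 16 week difference; the listed model delivers the mean of the week 8 and week 16 differences. For a week 16 DAS28 effect of 0.8 the target ranges from 0.40 to 0.80 as the assumed week 8 effect goes from 0 to 0.8, and exceeds 0.8 if the effect wanes.

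Equal weighting is exact only with complete data. The size of the discrepancy rests on a week 8 effect that the article does not give; it is zero if the effect is constant over the two visits. Power could move either way, so the case rests on what is estimated, not on power or type I error. It matters because the primary result would carry the name of an endpoint that it does not measure. The wording should be settled before the groups are compared.

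**What to change.** Add visit (8, 16 weeks) and group-by-visit to the listed fixed effects, keeping baseline and the random subject effect. Baseline-by-visit is optional. State that the baseline-adjusted group difference at week 16 is the single primary contrast and that week 8 is supportive. Apply the same to secondary outcomes measured at both visits. If the full protocol already contains these terms, saying so is enough.

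The alternative is to redefine the endpoint as the average over weeks 8 and 16. That makes text and model agree, but it changes the declared primary endpoint of a trial already under way.

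The preferred change costs one sentence and no new data. Its price is precision: if the effect is nearly complete by week 8, the week 16 contrast has less power than the average (0.75 against 0.84–0.86 when the effect is equal at both visits, under the assumptions above).

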#### Secondary outcome measures

Secondary outcomes are the same for all groups in the three RCTs: RA, ACPA-positive arthralgia, and MSOA, unless otherwise specified. Quality of life-related outcomes measured are self-reported physical, mental and, social health, using the validated Dutch-Flemish Patient Reported Outcomes Measurement Information System (PROMIS®) [53]. In order to select the most important secondary patient reported outcomes, we consulted the *Ambassadors*. From a list of 13 physical, mental and social item banks (see supplement 5), they chose physical function, fatigue, and pain interference as most important. We added depression to this list, since it is strongly associated with the onset of RA [7, 24]. Other secondary outcomes are waist circumference, fat mass (measured by dual-energy X-ray absorptiometry [DEXA]), blood pressure, LDL, HDL, triglycerides, fasting glucose, and ESR.

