## Discussion

The present paradigm of RA treatment is early recognition and prompt suppression of inflammation with drug therapy targeted to achieve and maintain remission or low disease activity [40]. Despite the success of intensified drug therapies, there are still unmet needs. Thirty percent of RA patients do not respond to the preferred medication, suffer from side effects, or become resistant to medication [63]. Also, 69% of RA patients are still limited by pain, fatigue, and reduced mobility [64], and the mortality gap between RA patients and the general population remains despite early aggressive treatment [65]. The unmet needs of RA patients, in combination with the underuse of the present knowledge of environmental risk factors for RA in clinical practice, call for an increased effort to investigate potentially effective non-pharmacologic options in the treatment of these diseases.

On the other hand, while treatment of OA comprises exercise treatment, weight loss, and mental health interventions, these lifestyle-related recommendations lack specificity and consensus [66].

The present protocol is in line with the gaps identified by the EULAR committees. For both RA and OA, more evidence on non-pharmacological interventions is needed with an emphasis on *multidisciplinary* approaches, including physical therapy and exercise, psychological support, and diet [66, 67].

A good example of a lifestyle program in which all these non-pharmacological disciplines are combined is the Ornish Program (USA, covered by most health insurance companies), based on a WFPD, exercise, and stress management. It has been shown to be effective for the treatment of coronary heart disease [28]. Since atherosclerosis and synovitis share pathological features [36, 68] and both RA as well as OA patients are at increased risk for cardiovascular disease, it is worthwhile to not only study the effect of this program on arthritis, but also on the factors that determine the risk of coronary heart disease.

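### Twelve secondary outcomes per RCT are each called significant at P < 0.05 under the primary outcome's rule, with no order among them and no supportive label

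*Protocol article*

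**What the plan says.** The Statistical analysis section of the Protocol article names the secondary outcomes as "physical function, fatigue, pain interference, depression, waist circumference, fat mass, blood pressure, LDL, HDL, triglycerides, fasting glucose and ESR". That is 12 items. It says that they "will be analyzed the same way as the primary outcomes. Statistical tests will be limited to primary and secondary outcomes", and leaves all remaining outcomes to descriptive statistics. The section closes, after the paragraph on the extension study, with a single unqualified threshold: P "values < 0.05 will be considered to be significant".

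The list is common to the three trials. The section on secondary outcome measures says: "Secondary outcomes are the same for all groups in the three RCTs: RA, ACPA-positive arthralgia, and MSOA, unless otherwise specified". It is carried forward as well: "In the extension study, the primary and secondary outcomes of the intervention study will become secondary outcomes, and adherence will be the primary outcome".

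The section on primary outcome measures names one main endpoint for each RCT: the DAS28, the RA-risk score and the WOMAC. The article states no testing order among the secondaries, does not make their tests depend on the primary result, gives no adjustment, and does not call them supportive or exploratory.

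**The concern.** The article is not silent here. It says which outcomes are tested, with which model and at which threshold, and it puts the secondaries on the tested side together with the primary. Taken literally, any of 12 results per RCT may be declared significant on the same terms as the primary, whatever the primary shows.

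Two consequences follow. An RCT with no effect on any secondary would still have a sizeable chance of reporting at least one significant secondary, in either direction. And if a primary failed, a secondary at, say, P = 0.04 could be reported beside it under the same rule. The same holds in RCT 2, which the sample size section describes as a pilot group of 16, and in the extension study, which is observational.

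**Working it through.** The article states no family-wise error rate, so there is no figure of its own to reproduce. The check asks what its rule implies.

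**Inputs from the Protocol article**
- Threshold per test: 0.05 (Statistical analysis). Whether tests are one- or two-sided is not stated; two-sided is assumed below.
- Number of secondary outcomes per RCT: *m* = 12 (Statistical analysis). If blood pressure is tested as systolic and diastolic, *m* = 13; that split is an assumption.
- Correlation between the test statistics: not given, so a range is shown.

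One test per outcome is counted, because the described model has a single group effect. Separate tests at 8 and 16 weeks and the additional per-protocol analyses are left out; both could only add to the count. The calculation covers the RCTs, not the within-subject extension analyses.

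**Step 1: independent tests, no true effect on any secondary**

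P(at least one false positive) = 1 − (1 − 0.05)^*m*
- *m* = 12: 1 − 0.95^12 = 1 − 0.540 = 0.460
- *m* = 13: 1 − 0.95^13 = 0.487

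Expected number of false positives for *m* = 12: 12 × 0.05 = 0.6. This does not depend on the correlation.

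**Step 2: equally correlated tests**

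With normal test statistics sharing a common correlation *r*,

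P = 1 − ∫ φ(u) · [Φ((1.96 − √r·u)/√(1−r)) − Φ((−1.96 − √r·u)/√(1−r))]^12 du

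| Assumed *r* | P, 12 tests |
|---|---|
| 0 | 46.0% |
| 0.3 | 39.7% |
| 0.5 | 31.9% |
| 0.8 | 18.6% |

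**Step 3: a less uniform pattern**

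Equal correlation among patient-reported scores, lipids, body composition and ESR is a simplification. As a check, the outcomes were grouped into the four PROMIS scores, waist and fat mass, the three lipids, and blood pressure, glucose and ESR singly. Simulation with 500,000 draws gave the following, again with assumed correlations:

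| Within group | Between groups | P, 12 tests |
|---|---|---|
| 0.5 | 0 | 42.4% |
| 0.5 | 0.2 | 40.3% |
| 0.6 | 0.2 | 39.0% |
| 0.7 | 0.3 | 35.3% |

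These fall inside the range of Step 2.

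**Step 4: the primary**

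Each RCT's primary is a separately named endpoint. Testing secondaries beside it does not change the probability that the primary is falsely significant, which stays at 5%.

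**The case against.** The strongest objection is that multiplicity handling for secondary outcomes is commonly left to a statistical analysis plan. Only a condensed article is shown, and 0.05 is a generic per-test threshold with no family-wise promise attached. This has weight: the lack of an adjustment method would not be a finding by itself, and no stated error rate is contradicted. It does not remove the point, because the article fixes a rule. A later plan that called the secondaries supportive would have to qualify the threshold sentence as it stands.

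It is also fair to say that the article is structured. It has primary, secondary and other tiers, it bases the sample size on the DAS28 and WOMAC only, and it keeps all other outcomes descriptive. What is missing is an order among the secondaries and a statement of what their P values are for.

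Several stronger readings are tempting, and the documents do not support them:
- A reader might infer that the primary's error is inflated. It is not (Step 4).
- A reader might quote a single family-wise figure such as 32%. That needs a correlation of about 0.5 across all 12 outcomes, which the article does not give.
- A reader might add up the error over RCT 1 and RCT 3. These are separate trials in separate populations, each with its own primary, so a pooled total has no bearing on either.
- A reader might infer from the Discussion that the cardiometabolic secondaries are meant to carry a conclusion. On risk factors for heart disease it says only that "it is worthwhile to not only study the effect of this program on arthritis, but also on the factors that determine the risk of coronary" …, and the Conclusion section names none of those outcomes.
- A reader might take the Ambassadors' choice as a ready testing order. They chose three PROMIS item banks from a list of 13, without an order among the three and without comparison to lipids, waist or glucose.

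**Conclusion.** The point holds for the secondaries. As written, the rule gives a 46% chance of at least one false significant secondary per RCT if the 12 tests are independent, and about 40% to 19% for assumed equal correlations of 0.3 to 0.8. All figures assume that no secondary is truly affected and that each is tested once, two-sided, at 0.05. Even the lowest value is well above 5%, so the conclusion does not depend on a particular correlation. The primary conclusions of the three RCTs are untouched; what is affected is how much a significant secondary can be taken to show. This is an inexpensive improvement to a stated rule, not a flaw in the design.

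**What to change.** Restrict the P < 0.05 sentence to the single primary contrast of each RCT (DAS28, RA-risk score, WOMAC). Add that the secondary outcomes, including those of the extension study, are supportive and are reported as estimates with 95% confidence intervals, without significance claims. No alpha needs to be shared across the three RCTs.

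The cost is a sentence or two, with no extra patients, visits or data. The article describes the trial as still under way, so the wording could be settled before analysis. The downside is small: an isolated secondary P value below 0.05 could no longer be called significant.

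Holm's procedure over an RCT's secondaries, applied only after its primary is significant, is an option if formal secondary claims are wanted. It has a real price. At the strictest step the threshold is 0.05/12 = 0.0042 (critical value 2.865). A secondary with 80% power at 0.05 has an expected test statistic of 1.960 + 0.842 = 2.802, so its power there is Φ(2.802 − 2.865), or about 47%.

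### The extension-study model has no visit term, so no parameter in it equals the 0 to 24 month change in adherence that is its primary endpoint, and month 0 is not fixed

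*Protocol article*

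**What the plan says.** The Primary outcome measures section states: "Main endpoint for the 2-year extension study for all three groups is the change in adherence from 0 to 24 months". The adherence score is the mean of four equally weighted components, one of which is attendance at meetings.

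For the analysis, the Statistical analysis section says: "These outcomes are analyzed in the same way as the intervention study, using the baseline, halfway, and end measurements from the 16-week intervention program", and adds the visits at 6, 12, 18 and 24 months. That makes seven occasions. It then calls for a within-subject analysis by a "repeated measures mixed model with random effect for the subjects and fixed effects for baseline values".

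The trial model that serves as the template has a "random effect for the subjects and fixed effects for group (intervention or control) and baseline values for DAS28, RA risk-score, or WOMAC".

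The Design section starts the two-year extension when the 16-week programme ends. The analysis sets are intention-to-treat, with per-protocol analyses in addition.

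**The concern.** The endpoint is a change between two time points. A model can estimate it only if something in the model distinguishes those time points. Here the fixed effects are listed, and visit is not among them.

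In the randomised phase, leaving out visit still leaves a group coefficient, which can be read as a between-group difference averaged over weeks 8 and 16. The extension has no group comparison, so that fallback is gone. An intercept, a baseline slope and a subject effect remain.

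The extension exists to learn whether participants keep up the programme. An average that mixes supervised programme visits with later follow-up can hide a fall, or a rise, by month 24. The open choice of month 0 adds to this: change since the programme ended measures maintenance, while change since before the programme measures net gain. These are different questions and can have answers of opposite sign.

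**Working it through.** The plan gives no sample size, effect or standard deviation for the extension endpoint, so there is no stated figure to reproduce. The check is of the model against the endpoint.

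**Model as written.** For participant i at visit j, with baseline B centred:

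Y_ij = b0 + b1·B_i + u_i + e_ij

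With complete, balanced data the estimate of b0 is the average of the visit means. No term depends on j.

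**Model with visit.**

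Y_ij = g_j + b1·B_i + u_i + e_ij

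Here each visit has its own mean g_j, and the 24-month change is g_24 minus the month-0 mean.

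**Illustration.** Only the visit schedule comes from the document. The mean scores are assumed. Visits in order are programme start, week 8, week 16, and months 6, 12, 18 and 24.

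- Declining: 0.5, 1.0, 1.1, 1.0, 0.9, 0.8, 0.7
- Full relapse: 0.5, 1.0, 1.1, 0.9, 0.75, 0.6, 0.5
- Flat after week 8: 0.5, then 1.0 throughout
- Declining path with its four extension values in reverse order: 0.5, 1.0, 1.1, 0.7, 0.8, 0.9, 1.0

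*Month 0 at programme start* (average of the six later visits minus the first value, against month 24 minus the first value):

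- Declining: 5.5/6 - 0.5 = 0.42, against 0.7 - 0.5 = 0.20
- Full relapse: 4.85/6 - 0.5 = 0.31, against 0.5 - 0.5 = 0.00
- Flat: 1.0 - 0.5 = 0.50, against 0.50
- Reversed: 5.5/6 - 0.5 = 0.42, against 1.0 - 0.5 = 0.50

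*Month 0 at programme end* (average of the four extension visits minus week 16, against month 24 minus week 16; this assumes that the earlier programme visits are left out of the average):

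- Declining: 3.4/4 - 1.1 = -0.25, against 0.7 - 1.1 = -0.40
- Full relapse: 2.75/4 - 1.1 = -0.41, against 0.5 - 1.1 = -0.60
- Flat: 1.0 - 1.0 = 0.00, against 0.00
- Reversed: 3.4/4 - 1.1 = -0.25, against 1.0 - 1.1 = -0.10

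The declining and reversed paths give identical averages but month-24 changes that differ by 0.30, and the error changes sign between them. The averaged estimate therefore cannot tell a fall from a rise during the extension. On the declining path the true change is +0.20 or -0.40, depending only on which visit is called month 0.

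**Per-protocol set.** A simulation assumed 160 participants (the planned RA plus OA total), a between-subject SD of 0.15 and a within-subject SD of 0.12. Keeping the upper half on mean extension adherence shifted the 24-month change by about +0.02. Keeping the upper half on the month-24 score shifted it by about +0.06. Selecting on an unrelated criterion shifted it by 0.00.

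**The case against.** The best defence is that this is a one-sentence summary in a condensed article. It speaks of a within-subject, repeated-measures analysis, names all seven occasions, and the endpoint is plainly a change over time. A statistician would probably add visit without being told, and an analysis plan that is not shown may do so. The intent is credible. But the article is not silent: it lists the fixed effects for a primary outcome, and the list does not fit the endpoint. The template model does not supply the missing term.

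It is also fair to say that this touches an observational extension and leaves the randomised comparisons alone.

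Two stronger readings are tempting, and the documents support neither.

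- A reader might infer that the per-protocol analysis selects on adherence and so conditions the outcome on itself. The article never defines that set by adherence. The only event that the Design section calls a deviation is a medication one (DMARD changes and intercurrent corticosteroids), and the extension meetings are optional. Per-protocol also only supplements intention-to-treat, so it could not invalidate the main estimate. The absence of a definition is not a finding in a condensed article.
- A reader might infer that the two-year result will be biased upwards because adherence fades. Nothing in the documents gives the trajectory. A flat path gives no discrepancy, and a rising extension path gives one in the other direction.

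**Conclusion.** The point holds as a mismatch between a stated model and its own endpoint. Followed literally, the extension analysis returns a visit-averaged level of adherence and no estimate of the 0 to 24 month change, and month 0 can be read in two ways.

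That the average differs from the month-24 value whenever adherence varies over follow-up (coincidence apart) follows from the text. How far it differs, and in which direction, does not. Over the four assumed paths the averaged change differs from the true change by 0 to about 0.3 score units in absolute size, and those figures illustrate the mechanism without predicting the trial's result. They also assume complete, balanced data; with missed visits the weights in the average would shift.

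No fault is established in the per-protocol analysis. It calls for a precaution only.

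**What to change.** In the extension paragraph of the Statistical analysis section:

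- Enter visit as a categorical fixed effect, with a random effect for subject.
- Name month 24 minus month 0 as the primary contrast.
- State that month 0 is the end-of-programme visit, which is where the Design section starts the extension. If month 0 is one of the modelled responses, do not also enter it as a covariate.
- Make any contrast with pre-programme values secondary, and say how the attendance component is handled. Attendance cannot be earned before the programme starts, so a quarter of the score's weight is then structurally zero or missing.
- If a per-protocol analysis is kept for the adherence outcome, define its set without using the adherence score.

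The trial outcomes that become secondary outcomes in the extension are analysed with the same model, so the visit term should apply to them too. The cost is a few sentences of wording. The visit schedule and the data collected do not change.
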